### Methods for Minimizing Bias

To minimize *selection bias* eligible participants will be randomly assigned to either the NH-CBT or the active control group in a 1:1 ratio using a block randomization strategy (8 blocks with 20 and 1 block with 12 participants). Randomization will be conducted by a research associate not affiliated with the study. The randomization scheme will be generated by using the website randomization.com which applies a pseudorandom number algorithm (http://www.randomization.com). Group allocation will be provided in sealed opaque sequentially numbered envelopes. The principal investigator (MR) and therapists involved in the study will not be masked to the results of the randomization, however the outcome assessors will be blinded to minimize *detection bias*. Before each of the follow-up interviews, participants will be clearly instructed not to discuss treatment content or the identity of their therapists with their assessor. After each follow-up assessment, the blinding of the outcome assessor will be checked with several self-report items (e.g., “Please guess which condition the participant was in”). In the case that the blinding of an outcome assessor cannot be ensured, the three assessor-rated measures will be re-done by a fully blinded assessor. Individual rehabilitation staff will deliver only one of the interventions, either NH-CBT or the control treatment, to reduce the risk of *contamination bias*. Participants from different treatment groups will not be treated in the same room/gym at the same time. Most of our participants will undergo an outpatient treatment and it will be less likely that we have several patients with FNSD receiving inpatient treatment at the same time. It is therefore less likely that participants will communicate with each other about the course of their treatment. Inpatient participants will be instructed not to discuss the details of their treatment with other patients, and inpatient rehabilitation staff will be instructed to remind inpatients of this. To minimize *reporting bias* the study is registered and all pre-specified outcomes are published under the Australian New Zealand Clinical Trials Registry (ANZCTR; identifier: ACTRN12620000550909). To minimize *bias due to loss to follow-up* participants will be sent text reminders on the morning of their appointments. Participants will be considered a dropout when they miss more than two sessions without calling first. Travel costs are not provided directly by the trial but can be reimbursed by other agencies under certain circumstances. Participants will be supported in accessing these reimbursements when eligible.

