The first part of the *psychological assessment* is a clinical interview where the principal investigator (MR) will provide individuals interested in participating with more detailed information about the study. We will explain to potential participants that we will offer them one of two treatments: one is conventional and more commonly used for individuals with FNSD, and has been found to be effective; and the other is new, and we are yet to establish evidence of its efficacy. Participants will be blinded to details of the content and proposed mechanisms of NH-CBT and the control treatment, and to differences between both treatments. They will only be informed that the core component of both treatments will be movement retraining, delivered by a rehabilitation professional. During the first part of the psychological assessment we will assess whether individuals meet all eligibility criteria and will ask them to give written consent to participate. In the second part, an assessor who is independent of this study and trained in applying the assessment tools will do the *baseline assessment*. The research assistant will do the Simplified Functional Movement Disorder Rating Scale (S-FMDRS) (30), the Functional Mobility Scale (FMS) (31) and the 10 m-Walk Test (32) with the participant. A physiotherapist will be present to ensure the safety of the participant. Participants will complete a baseline questionnaire including questions about demographic variables and all other outcome measures (see *Outcomes and Assessments*).

Participants will then be randomly assigned to receive either NH-CBT or the active control treatment over the following 8 weeks. At the end of the intervention period (*8-week follow-up*) participants will attend another assessment with an independent, blinded assessor and will complete all outcome measures. Sixteen weeks after baseline, participants from both groups will complete all outcome measures again (*16-week follow-up*). At that point, participants in the control group who have not achieved symptom remission will be offered NH-CBT and will be asked to complete a final questionnaire after 8 weeks of treatment (*24-week follow-up*).

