
### Data and Patients' Safety Monitoring

Participants with any type of neurological diagnosis with a range of associated physical disabilities (e.g., weakness, balance difficulties) are at some risk of falling. According to clinical observations, people with FNSD/PMD are at lower risk of injury than people with neurological damage (16). However, there are still some incidents with this group. Treatment necessarily involves taking managed risks whilst ensuring safety, using management strategies and mobility aids. All trial participants will be assessed by a physiotherapist as they start the movement retraining part of the treatment (see *Interventions*) and throughout the treatment if needed, to ensure adequate steps are taken to ensure safety. In the case of serious adverse events (SAE) the Severity Assessment Code (SAC) rating for adverse event reporting (33) will be completed by the therapist. The study therapist has to contact the principal investigator (MR) within 24 h after the event. The PI will not be blinded to the result of the randomization and will therefore be able to decide if the SAE was a serious adverse reaction to the trial treatment.

In order to monitor and supervise the progress of the trial and SAEs associated with the trial treatment, an independent Data Safety and Monitoring Board will be involved, including a psychiatrist, a statistician, a manager of the ISIS Centre and a person who was formerly treated for FNSD at ISIS as a stakeholder of patients' interests. The DSMB will meet on a regular basis and will make final decisions to terminate the trial prematurely for harm, based on their monitoring and evaluation of SAE attributed to our treatment. The SAC rating for adverse event reporting allows for differentiation of four levels of severity of adverse events (34). In the case of severe and major events (SAC 1 and 2), the trial would have to be suspended with immediate effect pending investigation. The DSMB will discuss SAC 3 and 4 events (minor to moderate events), how they relate to our treatment and how they will influence the further course of this trial. The DSMB will also make final decisions to terminate the trial prematurely for benefit, based on stopping rules and interim analyses described below (see *Sample size, power calculations, and interim analyses*).

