Besides the strengths, we anticipate several limitations. We have already discussed risks of bias and have implemented tools to reduce these risks. There are additional challenges that we anticipate with implementing the study procedure. First, recruiting from one hospital can limit the representativeness of our sample and can hamper the potential to gain the optimal sample size. The institution where we will conduct our trial covers the neurological rehabilitation of a substantial part of the NZ population, which will ensure our sample is largely representative for the region. We first want to ensure the feasibility of our trial at this site before considering the potential to extend the trial to at least one other site. With a priori planned interim analyses, we will regularly check if the conservative estimation of our optimal sample size will need correction. Second, the design of our active control intervention has several advantages mentioned above. Nonetheless, we have to expect indirect therapeutic effects of our active control treatment (e.g., incidental change in beliefs after re-establishing a normal movement). Even accounting for the active control treatment being potentially less effective than NH-CBT, it seems likely that the mean difference between groups will be small. Our power analysis therefore builds on a conservatively estimated small between-group effect. When designing the control intervention, we also had to consider the pragmatic fact that a treatment-as-usual or a waitlist control group would not have been feasible, because our institution is the only one covering neurorehabilitation for patients from a bigger district in New Zealand, implying limited resources and long waitlists for receiving treatment. Third, another pragmatic limitation is that we have to accept participants in the inpatient and outpatient settings as well as participants of older ages. We will apply statistical strategies to control for the type of treatment setting in our data analysis. We will include older participants only if motor symptoms are considered highly likely to be functional and not related to age-related degenerative processes. Fourth, our 8-week follow-up window after the end of treatment is very short. Again, due to pragmatic reasons associated with delivering both treatments in the context of a clinical service, we would not be able to let our control participants wait for a longer period than this before they receive NH-CBT. At the same time, we consider the *controlled* follow-up assessment as an important strength of our study design. Finally, we will implement several methods to ensure treatment fidelity (e.g., frequent supervision, audio-recording the initial therapy session, and feedback to therapists). However, we will not be able to completely exclude the risk of therapists deviating from our rules of treatment fidelity and exposing participants to distraction techniques or interventions that address illness beliefs.

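### Fixed, published block lengths let an unmasked recruiter know about 16 of 172 allocations in advance; the promised control for treatment setting is missing from the stated model

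*Protocol article*

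**What the plan says.** Methods for Minimizing Bias describes 1:1 allocation by a "block randomization strategy (8 blocks with 20 and 1 block with 12 participants". No stratification factor is named. On concealment, the same section says "Randomization will be conducted by a research associate not affiliated with the study" and "Group allocation will be provided in sealed opaque sequentially numbered envelopes".

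That section also says that the principal investigator and the "therapists involved in the study will not be masked to the results of the randomization". Data and Patients' Safety Monitoring repeats the point: "The PI will not be blinded to the result of the randomization".

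Under Study Design and Procedure, the principal investigator gives interested patients the detailed trial information in a clinical interview, the first part of the psychological assessment. In that part, "we will assess whether individuals meet all eligibility criteria and will ask them to give written consent to participate". An independent assessor then does the baseline assessment, and randomisation follows. Table 1, item 5, names the principal investigator as the psychologist who delivers the NH-CBT psychoeducation.

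On setting, the Discussion states: "We will apply statistical strategies to control for the type of treatment setting in our data analysis". Statistical Analysis lists the model terms as baseline adjustment, time, group and group-by-time.

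**The concern.** Concealment has two parts: nobody can read the next assignment, and nobody can work it out. The envelopes and the outside associate secure the first. Fixed lengths in the public domain weaken the second. At one site, the principal investigator meets every candidate and personally gives the opening session to the NH-CBT arm, so the running tally of both arms is available without breaking any envelope. Once one arm has filled its half of a block, every remaining place in that block is known.

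Foreknowledge at the eligibility and consent interview can affect who is enrolled and when, without any bad faith. Several exclusion criteria call for judgement, for instance whether a mental health condition might affect participation. Table 2 does not mark the primary outcome, the SF-36 Physical Functioning subscale, as a blinded assessor rating. In any case, assessor blinding does not correct a case mix that differs between arms.

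The setting point is separate and smaller. One section commits to an adjustment, and the section that defines the model does not contain it. The form of the adjustment therefore stays open in a trial with repeated efficacy looks.

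**Working it through.** **Inputs.** Block lengths and 1:1 ratio: Methods for Minimizing Bias. Sample size of 172: Sample Size, Power Calculations, and Interim Analyses. Assumptions: the recruiter knows all past allocations, the block lengths and the position of the block of 12. The article does not state that position.

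**The plan's own figure.** 8 × 20 + 12 = 172. This matches the planned recruitment (164 before dropout; 164 × 1.05 = 172.2 and 164/0.95 = 172.6). The nine blocks use up the whole sample as one list.

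**Certain allocations.** In a block of 2m with m places per arm, the determined places are the final run of a single arm. On average m/(m+1) NH-CBT places follow the last control place, and the reverse is equally likely, so the expected number is 2m/(m+1).

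- Block of 20 (m = 10): 20/11 = 1.82
- Block of 12 (m = 6): 12/7 = 1.71
- Total: 8 × 1.818 + 1.714 = 16.3, and 16.3/172 = 9.5%

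The last place in each block is always determined, so the minimum is 9. A simulation of 5,000 lists gave a mean of 16.3, with 95% of lists between 11 and 24.

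**Best-guess accuracy.** Guessing the arm with more places left gives m + (4^m / C(2m,m) − 1)/2 correct guesses per block.

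- m = 10: 10 + (5.675 − 1)/2 = 12.34
- m = 6: 6 + (4.433 − 1)/2 = 7.72
- Total: 8 × 12.338 + 7.716 = 106.4, and 106.4/172 = 61.9%

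**Alternative schemes** (simulated; the recruiter knows the set of possible lengths but not their order):

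| Scheme | Certain allocations of 172 | Best guess correct |
|---|---|---|
| Plan: 8 × 20 + 12 | 16.3 (9.5%) | 61.9% |
| Lengths drawn from 12, 16, 20 | about 2 (1.2%) | about 62% |
| Lengths drawn from 4, 6, 8 | about 4.3 (2.5%) | about 68% |

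Varying large lengths removes most of the certainty. It does not change the general guessability, and short blocks make that worse.

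**Setting.** The stated outcome of interest is the group-by-time interaction, with time coded as contrasts to baseline. Suppose setting s enters only as a main effect δs, the same at every visit. The change from baseline to week 8 then contains δs − δs = 0, so the term cancels. In a complete-data simulation with N = 172 and an unstructured covariance, the week-8 interaction was 0.684 (SE 0.151) both with and without a setting main effect. An adjustment that can alter this contrast needs a setting-by-time term. This takes baseline as one of the repeated responses, as the contrasts to baseline imply. If baseline were only a covariate, a main effect would not cancel.

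**The case against.** The case for leaving the plan alone has several sound parts.

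- **Safeguards.** Patients are admitted consecutively and a neurologist makes the diagnosis and the first judgement of eligibility. Eligibility, consent and the baseline assessment all precede allocation. A reader might infer that eligibility is left open until the arm is known; the stated order rules that out. What remains is foreknowledge at the interview itself.
- **The principal investigator's role.** The article uses the plural for the eligibility assessment, so sole responsibility is an inference. The conduct of the interview and the lack of masking are stated.
- **Guessability.** A reader might blame the roughly 62% best-guess rate on fixed, published lengths. That is not supported: the rate is 61.9% under the plan and about 62% with undisclosed lengths drawn from 12, 16 and 20. It belongs to permuted blocks of this size. Only the certain places are due to the fixed lengths.
- **Size of bias.** A reader might convert the certain places into a share of the treatment effect. That needs an assumed prognostic shift per exploited place, which the article does not give. It would also have to allow for baseline adjustment, which absorbs much of any selection on visible baseline severity.
- **Setting.** Stratification is optional, and with mostly outpatients it risks an unfilled inpatient block. Its absence is a design choice. The article does not call setting a marker of severity, and for this model a loss of precision from omitting it is not shown. The exact form of adjustment may sit in an analysis plan that is not shown. The two sections of the article still disagree.

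**Conclusion.** The point holds in a limited form. With published fixed lengths, a single site and an unmasked principal investigator at the eligibility and consent interview, about 16 of 172 allocations (9.5%) can be known with certainty beforehand. This is the upper figure: it assumes a complete tally and a known position for the block of 12. It measures opportunity and does not show that bias will occur. The risk is modest because the blocks are large and other safeguards are in place, but it is avoidable at little cost.

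On setting, the finding is a mismatch between the Discussion and Statistical Analysis. The documents do not support going further, to a claim that the trial must stratify or that the primary analysis loses power.

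**What to change.** **Allocation.** For all places not yet assigned, have the independent associate generate a new list with block lengths varied at random but similarly large, for example drawn from 12, 16 and 20. Withhold the lengths from recruiting staff and from publications until recruitment ends. Do not shorten the blocks. If guessability near 62% is itself unacceptable, simple randomisation is the only option considered here that removes it.

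**Setting.** Record planned setting (inpatient or outpatient) before the envelope is opened. Name it in the model under Statistical Analysis together with its interaction with time, so that the section matches the Discussion. Setting recorded after allocation should not be used, because the arm could influence it.

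**Cost.** One new list, one baseline field and the added model terms; the sample size stays at 172. The downside is a small possible arm imbalance at interim looks. If a block of 20 comes first, the present list guarantees a difference of at most 2 at the look after 22 participants (one full block plus 2), and it ends at exactly 86 per arm. Random lengths give up both guarantees.

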
### Data and Patients' Safety Monitoring

Participants with any type of neurological diagnosis with a range of associated physical disabilities (e.g., weakness, balance difficulties) are at some risk of falling. According to clinical observations, people with FNSD/PMD are at lower risk of injury than people with neurological damage (16). However, there are still some incidents with this group. Treatment necessarily involves taking managed risks whilst ensuring safety, using management strategies and mobility aids. All trial participants will be assessed by a physiotherapist as they start the movement retraining part of the treatment (see *Interventions*) and throughout the treatment if needed, to ensure adequate steps are taken to ensure safety. In the case of serious adverse events (SAE) the Severity Assessment Code (SAC) rating for adverse event reporting (33) will be completed by the therapist. The study therapist has to contact the principal investigator (MR) within 24 h after the event. The PI will not be blinded to the result of the randomization and will therefore be able to decide if the SAE was a serious adverse reaction to the trial treatment.

In order to monitor and supervise the progress of the trial and SAEs associated with the trial treatment, an independent Data Safety and Monitoring Board will be involved, including a psychiatrist, a statistician, a manager of the ISIS Centre and a person who was formerly treated for FNSD at ISIS as a stakeholder of patients' interests. The DSMB will meet on a regular basis and will make final decisions to terminate the trial prematurely for harm, based on their monitoring and evaluation of SAE attributed to our treatment. The SAC rating for adverse event reporting allows for differentiation of four levels of severity of adverse events (34). In the case of severe and major events (SAC 1 and 2), the trial would have to be suspended with immediate effect pending investigation. The DSMB will discuss SAC 3 and 4 events (minor to moderate events), how they relate to our treatment and how they will influence the further course of this trial. The DSMB will also make final decisions to terminate the trial prematurely for benefit, based on stopping rules and interim analyses described below (see *Sample size, power calculations, and interim analyses*).

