### Interventions

#### Structure, Providers, and Treatment Fidelity

Participants in both study groups will first receive an explanation of their functional motor symptoms by their neurologist, as part of the *neurological assessment* (described earlier under *Study Design and Procedure*). The main part of the intervention in both groups will start with an initial 60–90 min session that includes education of participants. In both groups, this initial session will be followed by a minimum of 2 up to a maximum of 23 sessions of movement retraining and one final session of relapse prevention. Differences between the groups in the content of the initial session, the movement retraining and the relapse prevention are described below. Sessions will last between 30 and 120 min and will be delivered face to face over 8 weeks. The frequency and scheduling will depend on participants' individual needs (e.g., type and severity of symptoms) and stamina. (see Criteria for finishing the movement retraining before a maximum of 23 sessions can be found in Table 1 under “8. When and how much”. Sessions will follow a treatment manual and will take place either as an inpatient or an outpatient treatment. For both interventions, the initial education session will be conducted by a licensed clinical psychologist, and the movement retraining will be delivered by a licensed rehabilitation professional (physiotherapist, occupational therapist, rehabilitation assistant), but will necessarily involve physiotherapist oversight and involvement at some point. Gender, age, professional backgrounds, and years of experiences of the neurologists, clinical psychologists, and rehabilitation professionals delivering the NH-CBT and the control intervention will be recorded in the main trial paper. Table 1 outlines details of Nocebo-Hypothesis Cognitive Behavioral Therapy (NH-CBT) and the active control treatment (supportive counseling and movement retraining), as well as the means of ensuring treatment fidelity, according to the TIDieR checklist (37).

**Table 1 T1:** Nocebo-Hypothesis Cognitive Behavioral Therapy and supportive counseling and movement retraining (active control intervention) described following the TIDieR checklist.

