	*NH-CBT relapse prevention (1 session)*: The treatment cycle is taken as far as possible in the final session. Therapist and participant collaboratively set a final movement goal that is as high as the participant wishes. The participant then tries to achieve it. The second part of the relapse prevention stage gives clear advice to people about what to do if symptoms re-emerge in future. For each individual person, a personalized behavioral experiment is devised that will prove to participants that their most feared neurological event is not happening. This experiment involves them reminding themselves that minor transient symptom, often referred to as “glitches”, are harmless and are just the subconscious expressing a momentary doubt via a nocebo effect.	*Control relapse prevention (1 session)*A self-management plan is introduced to the participant, including a summary of useful strategies that help to normalize movement, activity plans to address boom and bust patterns and how to progress activity, future goals, and what to do on difficult days and during periods of symptom exacerbation. Therapists are instructed to avoid making any suggestions that state or imply the role of illness beliefs.
5. Who provided	*Neurological assessment:* All neurologists involved in this trial will be employed on consultant level. They will receive training from the PI (MR) in person or by telephone. They will have been given suggestions by Stone (29) of how to explain FNSD/PMD to participants.	
	*NH-CBT psychoeducation*: clinical psychologist (PI: MR)	*Psychological input and supportive counseling*: clinical psychologist (other than PI)
	*NH-CBT movement retraining*: licensed rehabilitation professional (physiotherapist, occupational therapist, rehabilitation assistant), with a physiotherapist always having a role in developing the treatment plan (including safety management plan) and having oversight of the physical elements of the treatment	*Control movement retraining*: licensed rehabilitation professional (physiotherapist, occupational therapist, rehabilitation assistant), with a physiotherapist always having a role in developing the treatment plan (including safety management plan) and having oversight of the physical elements of the treatment

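### An unblinded PI who provides part of one arm judges whether serious events are treatment reactions, and the board's harm decision is worded around attributed events without saying whose attribution counts

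*Protocol article*

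**What the plan says.** Under Data and Patients' Safety Monitoring, the treating therapist completes the SAC rating for an SAE and must contact the PI within 24 hours. On causality the section says: "The PI will not be blinded to the result of the randomization", and it continues that the PI "will therefore be able to decide if the SAE was a serious adverse reaction to the trial treatment". The board's decision to end the trial early for harm is then described as "based on their monitoring and evaluation of SAE attributed to our treatment".

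The same section treats events by grade. A SAC 1 or 2 event suspends the trial at once while it is investigated, and no relatedness condition is attached. For SAC 3 and 4 events the board itself discusses the relation to treatment and the consequence for the trial.

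Table 1, item 5, lists the provider of the NH-CBT psychoeducation as "clinical psychologist (PI" and the provider of the matching control session as "clinical psychologist (other than PI". In both arms, "the movement retraining will be delivered by a licensed rehabilitation professional (physiotherapist, occupational therapist, rehabilitation assistant". Under Methods for Minimizing Bias, the PI and the "therapists involved in the study will not be masked to the results of the randomization".

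A footnote to Table 2 ties use of the SAC to the eight weeks of NH-CBT. The safety section sets no such limit by arm.

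**The concern.** The text presents knowledge of the allocation as what equips the PI to judge causality. For a causality judgement, that knowledge is the usual route by which expectation enters. Here the person judging also has a treatment role in one arm and not in the other.

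This matters because the termination decision is worded around attributed events. If the PI's judgement is the attribution meant, an SAE in the NH-CBT arm that the PI calls unrelated falls outside the stated basis for ending the trial. The section itself says that treatment involves managed risks and that falls can happen. A fall can reasonably be put down either to the disorder or to the session, so attribution will often be a matter of discretion for the events most to be expected. At stake is whether a difference in harm between the arms would reach the board undiluted.

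**Working it through.** No arithmetic applies: the article states no SAE rate, no numerical harm boundary and no rule for turning events into a decision. The check is a comparison of what the sections say.

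1. **Who judges causality.** The safety section names the PI and gives unblinding as the reason. It names no second or blinded causality assessor at that step. The severity grade comes from the treating therapist, who is also unmasked.

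2. **Where that person stands.** By Table 1, item 5, the PI gives one component of NH-CBT, the psychoeducation session, and not its control counterpart. The 2 to 23 movement retraining sessions in either arm are given by rehabilitation professionals. The PI's role as a provider is therefore partial, but it lies in one arm only.

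3. **What the board acts on.** The termination-for-harm sentence gives the evaluation to the board but restricts its object to attributed SAEs. The sentence on the board's remit is similar: it speaks of SAEs associated with the trial treatment. Neither sentence says who makes the attribution or association.

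4. **What happens at each grade.**
   - SAC 1 and 2: immediate suspension, no relatedness condition. Who investigates is not stated, and no causality assessor other than the PI is named. The later decision to terminate is still worded around attributed events.
   - SAC 3 and 4: the board discusses relatedness itself, so a view independent of the PI is stated.

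   Independent discussion of relatedness is thus stated for the minor-to-moderate grades and not for the most serious ones.

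5. **Comparison with the outcome ratings.** Under Methods for Minimizing Bias, outcome assessors are blinded, the blinding is checked after each follow-up assessment, and the assessor-rated measures are repeated by a fully blinded assessor if it cannot be ensured. No comparable protection is described for SAE causality.

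6. **Capture by arm.** The Table 2 footnote, read literally, applies the SAC only to NH-CBT. The safety section reads as covering all trial participants. If the footnote governed, SAEs in the control arm would not be graded in the same way, and a comparison by arm would lack a like-for-like comparator.

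**The case against.** The strongest reply is that the harm decision belongs to the board, and that the text refers to the board's own monitoring and evaluation. A reader might infer that the PI alone filters what the board sees, or that the whole harm signal passes through the provider of the experimental treatment. The article does not say this. It does not define attributed as attributed by the PI, and it does not say that events judged unrelated are withheld. Each SAC grade also has a route with no stated condition on the PI's opinion. That part of the objection stands: the plan is ambiguous here and does not establish a filter.

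A reader might also describe the PI as delivering NH-CBT as a whole. Table 1 does not support that. The physical risk the section describes arises mainly in movement retraining, which others deliver.

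It would likewise go too far to speak of a count of events that triggers stopping. None exists, so a probability of reaching some number of attributed events would rest on invented rates, attribution fractions and thresholds. Nor is the planned group comparison of adverse therapy effects affected by the PI's judgement: under Statistical Analysis it uses the Inventory for the Assessment of Negative Effects of Psychotherapy.

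Finally, this is a condensed article, and the detail of board reports may sit in a charter that is not shown. That is a fair reason not to call report formats or adjudication procedures missing. It does not answer the point, which rests on two things the article does state: who decides causality and why, and the restriction of the termination decision to attributed events.

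**Conclusion.** The point holds as a cheap improvement. The article fixes a causality judgement by an unblinded PI who provides part of one arm, offers the unblinding as its justification, and restricts the termination-for-harm decision to attributed SAEs without saying whose attribution counts. The suspension rule for SAC 1 and 2 and the board's discussion of SAC 3 and 4 reduce the exposure. They do not remove it, because the most serious grades have no named causality assessor independent of the PI and the final decision remains worded around attribution.

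The size cannot be stated from the document. How much it matters depends on how many SAEs occur, how often their cause is open to dispute, and whether the board in practice sees all of them; the article gives none of these. The conclusion assumes only that the sentences are applied as written. If a board charter already sends all SAEs from both arms to the board, what remains is to align the article's wording with it.

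**What to change.** Reword Data and Patients' Safety Monitoring to say that:

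- the board receives every SAE from both arms, whatever the PI's opinion on causality;
- the board bases its harm decision on all SAEs by randomised arm;
- the PI's attribution goes to the board as supporting information only.

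The 24-hour notification to the PI stays as it is. Delete the reasoning that unblinding is what enables the causality decision.

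Reconcile the Table 2 footnote on the SAC with the safety section, so that SAEs are captured equally in both arms.

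The cost is a few sentences of wording, carried into any board charter, and slightly more reading for the existing board members. No new committee, data collection or change to the sample size is needed.
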